**Methods**

Observational multi-center study of fluid administration in the ICU:s at two Swedish tertiary centers (Södersjukhuset and Danderyds Sjukhus) and one Australian university hospital (Austin Hospital). Planned recruitment of 100 adult patients.

Inclusion criteria: Admission to ICU. Age 18 years or older.

Exclusion criteria: Patients in whom death is considered imminent (within 24 hours). The intensive care physician declines to participate.

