Patients will receive standard care at the discretion of the treating physicians, including all measurements and monitoring. When the treating physician chooses to give a fluid bolus (defined as 250 mL or more of fluids over 30 minutes or less), the patient will be included and the physician asked to fill out a questionnaire asking for pre-defined reasons to give fluids: hypotension, tachycardia, oliguria, low central venous pressure (CVP), high lactate levels, low mixed venous oxygen saturation (SvO_2_) or central venous oxygen saturation (ScVO_2_) and low cardiac output (CO). Also, the physician will be asked to specify what hemodynamic response of these variables is expected at completion of the bolus and one hour later. The expectations and results of the first bolus after inclusion will be measured and any further boluses given to the same patient will not lead to re-inclusion and further questionnaire’s. The first bolus after inclusion will be studied, which can be at any time during the ICU-stay. For comparison, data will be extracted from the departmental documentation system (Clinisoft^®^, TakeCare^®^ or other methods) regarding MAP, pulse rate, CO, CVP, urine output and pertinent laboratory values such as lactate, SvO_2_ or ScVO_2_ and creatinine. Measurements will be registered before the onset of the fluid bolus and until 60 min after completion of the fluid bolus. If any other static or dynamic hemodynamic variables such as Pulse Pressure Variation (PPV), Stroke Volume Variation (SVV), Extravascular Lung Water (EVLW) or Stroke Volume Index (SVI) are being measured this data will be extracted as well. Any infusions of vasoactive medications and diuretics given will also be recorded and dosages registered will be accounted for as confounders for hemodynamic changes. Any fluids administered during the study period of besides those of the fluid bolus that led to inclusion will be recorded and accounted for as confounders. Fluids will be registered as colloids, crystalloids or maintenance fluids. For MAP, pulse rate and any hemodynamic variables values will be recorded according to the sampling in the electronic system. Laboratory values will be ordered at the clinicians’ discretions as usual (usually at admission and then as indicated clinically) and extracted at these intervals. Urine output will be recorded for six hours following the fluid bolus.

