**Statistical analysis**

The accuracy of the physicians’ estimations of the effect of a fluid bolus will be described using Bland-Altman methodology. In addition, clinicians’ ability to predict the hemodynamic response will be assessed by calculating sensitivity, specificity, PPV, NPV and the area under the receiver operating characteristics curve. Outcomes will be compared after log transformation where appropriate. Comparisons will be made using t-test and ANOVA for repeated-measures or Wilcoxon signed-rank test and Kruskal-Wallis test according to the underlying distribution for continuous data and Fishers’s exact test for categorical data. Multiple regression analysis will also be performed adjusting for predefined confounding factors associated with hemodynamic changes: change in vasopressors, sedatives, diuretics, change in pacemaker rhythm, additional fluid boluses.

Ethical considerations

Ethical approval will be sought from the Ethical Review Board of Stockholm and the Austin ethical review board.

Information will be posted on the study sites, and if objections are raised to inclusion patients will not be included.

Patients in Stockholm will be covered by Sweden’s Patient Insurance policy.

Data collected will be coded and treated confidentially

The study will be observational and no changes will be made in the care of the patients included. There are no foreseeable risks for the patients to be included in this study.

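### Repeated-measures ANOVA fits poorly with discretionary readings on no common time grid; a mixed model would keep partial data in the secondary haemodynamic comparisons

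*Protocol*

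**What the plan says.** Statistical analysis names "t-test and ANOVA for repeated-measures" for continuous data, with rank tests as the alternative according to the distribution of the data. The methods named there do not include a mixed model.

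Methods describes the data these tests will receive:

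- Patients receive "standard care at the discretion of the treating physicians, including all measurements and monitoring".
- For MAP, pulse rate and other haemodynamic variables, "values will be recorded according to the sampling in the electronic system".
- Laboratory values are ordered at the clinicians' "discretions as usual (usually at admission and then as indicated clinically) and extracted at these intervals".
- The period is bounded, but no times within it are fixed: "Measurements will be registered before the onset of the fluid bolus and until 60 min after completion of the fluid bolus".
- The bolus may last any time up to 30 minutes, so completion falls at a different interval from the start in each patient.

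The Aim section lists changes in CI, heart rate, blood pressure, CVP, lactate, ScvO2/SvO2 and urinary output as secondary outcomes. Sample size: "Planned recruitment of 100 adult patients".

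**The concern.** Classical repeated-measures ANOVA works on one complete row per patient at times common to all. The Protocol asks about completion and one hour later, so with baseline the natural row has three entries. Nothing in Methods ensures that all three exist, least of all for variables measured on indication or only in patients with the relevant monitoring.

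Two things are at stake. The first is lost data: a patient with two of three readings contributes nothing to the ANOVA. The second is selection: if a clinician repeats a lactate because the first response disappointed, patients with full rows are those who responded less, and the estimated changes are too small.

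The rank alternatives do not solve this. The signed-rank test needs complete pairs, and Kruskal-Wallis is a test for independent groups.

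**Working it through.** The Protocol gives no missing-data rate, SD or effect size, so there is no figure of its own to reproduce. From the Protocol come N = 100 and the three nominal times (before, completion, one hour later). Every other input below is an assumption.

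**1. Complete rows.** If each reading is missing independently with probability m, the expected number of complete rows is 100 × (1 − m)³.

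| m | Complete rows of 100 | If baseline is always present, 100 × (1 − m)² |
|---|---|---|
| 2% | 94.1 | 96.0 |
| 5% | 85.7 | 90.2 |
| 10% | 72.9 | 81.0 |
| 20% | 51.2 | 64.0 |
| 30% | 34.3 | 49.0 |
| 50% | 12.5 | 25.0 |

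Independence matters. If a variable is absent for whole patients because they are not monitored for it, 20% missing leaves 100 × 0.8 = 80 complete rows, and no model recovers the other 20.

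**2. Selection on the observed response.** Assume between-patient SD 8, residual SD 5, true changes +4 at completion and +2 at one hour, and half of the one-hour readings taken, more often after a poor first response. The two changes share the baseline error. The variance of the first change is 2 × 5² = 50 and its covariance with the second is 5² = 25, so bias in the first passes to the second at 25/50 = 0.5. Simulation, complete rows only:

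| Selection | Change at completion (true +4) | Change at one hour (true +2) |
|---|---|---|
| Mild | +2.8 | +1.4 |
| Moderate | +1.8 | +0.9 |
| Strong | +0.4 | +0.2 |

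The shortfalls (1.2 and 0.6; 2.2 and 1.1; 3.6 and 1.8) are in the expected 2:1 ratio. Using the observed earlier readings of all patients recovers about +2.0 at one hour in each case.

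**3. Selection on the level at completion.** With the same SDs and true changes +5 and +3, and a one-hour reading more likely after a low value at completion, about 50 of 100 rows are complete. Complete cases give a first change of 3.6 and a baseline of 61.4 (truth 5.0 and 65); the mixed model gives 5.0 and 65.0. The one-hour change is about 2.9 by either method, so which contrast is biased depends on the mechanism.

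**4. Selection on the unseen value.** If whether the one-hour reading is taken depends on that value itself, both methods fail: complete cases give 1.6 and the mixed model 1.0, against a true 3.0.

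**5. Sphericity.** Take correlations 0.9 (baseline–completion), 0.4 (baseline–one hour) and 0.5 (completion–one hour) with unit variances. The variances of the differences are 2(1 − 0.9) = 0.2, 2(1 − 0.4) = 1.2 and 2(1 − 0.5) = 1.0, which are far from equal (epsilon 0.63). The uncorrected 5% test runs at 7.4% with 40 patients and 7.2% with 100. With a Greenhouse-Geisser correction it runs at 5.1% and 4.9%.

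**The case against.** The strongest reply is that deletion is inferred. The Protocol states no missing-data rule and does not say how many times enter the ANOVA; such detail is commonly left to an SAP, which is not at hand. That stands as a limit. A reader might infer that the plan commits itself to dropping every patient with a missing reading and to ignoring every reading between the three times; the text says neither. What remains is that a method is named, and its usual form does not suit the data described.

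The same sentence also names the t-test and the signed-rank test. Used as a paired comparison of baseline with completion, either needs only two readings; under the mechanism in step 2 it recovers +4.0. The bias at completion therefore arises only where the three-time ANOVA supplies the estimate. A paired comparison at one hour does not escape, because the missing reading is one of its pair.

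MAP and pulse rate follow the sampling of the electronic system and are probably charted often enough to lose little. For CVP and CO/CI, absence may be by patient, where a mixed model adds nothing. For laboratory values, the reason for sampling may be unrecorded; step 4 shows the mixed model then doing worse than complete cases. These limits narrow the benefit without making the ANOVA the better choice.

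A reader might also take step 5 as a defect in itself. It rests on one chosen correlation pattern and disappears with a routine correction that the Protocol does not exclude.

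**Conclusion.** The point holds for the secondary haemodynamic comparisons. The named ANOVA presupposes complete rows at common times, and Methods describes data that need not have them. At assumed missingness of 5% to 30% per reading, about 86 down to 34 of 100 patients would remain. If sampling follows a poor observed response, the one-hour change could be roughly halved or nearly lost (+0.9 or +0.2 against +2). These sizes rest on assumed missingness, SDs and selection; the direction follows from the mechanism.

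The force lies with lactate, ScvO2/SvO2, CVP and CO/CI. It would be wrong to infer that the main result is at risk: the accuracy of the physicians' expectations is described by Bland-Altman methods and prediction measures, which this does not touch. Nor do the documents show that the bias will occur; they only make response-dependent sampling plausible by tying laboratory tests to clinical indication.

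**What to change.** In Statistical analysis, replace the repeated-measures ANOVA with wording such as:

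> Changes in haemodynamic and laboratory variables will be estimated with a linear mixed model fitted by REML, with Kenward-Roger or Satterthwaite degrees of freedom. Readings will be assigned by pre-stated windows to three times: before the bolus, completion, and one hour after completion. Time will be a categorical factor with an unstructured within-patient covariance. Patients with partial data will be included. Changes at completion and at one hour will be reported as model contrasts with 95% confidence intervals, with the number of patients contributing for each variable and time. The analysis assumes that missingness depends only on observed readings.

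Three details matter. A random patient intercept alone imposes compound symmetry, and on complete data it gives the same F as the ANOVA (both 0.0552 in a check), so it does not remove the sphericity problem. An unstructured covariance needs common discrete times, which is why the windows are required. Time should be anchored at completion, because the outcomes are defined from there.

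The cost is wording and standard software, with no new data and no change in care. The windows must be chosen before the data are seen, readings outside them are not used, and the missingness assumption must be stated as a limitation. The model adds nothing for a variable never measured in a patient.

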**Aim**

The aim is to investigate to what extent the expectations of the attending physician concerning hemodynamic effects from the infused fluid in the critically ill are met.

Primary outcome: To describe the accuracy and precision of the expectations of the clinicians of the effect of a fluid bolus at completion of the fluid bolus. Secondary outcomes: To describe the accuracy and precision of the expectations of the clinicians of the effect of a fluid bolus one hour after the completion of the fluid bolus. The reasons for fluid administration. Changes in hemodynamic variables (Cardiac Index (CI), heart rate, blood pressure, CVP,) and lactate, central/mixed venous saturation (ScvO2/SvO2) and urinary output.

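### The predefined confounder list for the regression omits site in a three-ICU, two-country study, and no by-site check of the primary outcome is described

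*Protocol*

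**What the plan says.** The Methods section of the protocol describes an "Observational multi-center study of fluid administration in the ICU:s at two Swedish tertiary centers" together with "one Australian university hospital (Austin Hospital", and gives the size as "Planned recruitment of 100 adult patients". It sets no target, minimum or maximum per site.

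On how patients are treated and measured, Methods says "Patients will receive standard care at the discretion of the treating physicians, including all measurements and monitoring". Observed values come from two named record systems or from other means, at whatever sampling interval the local system uses.

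The primary outcome in the Aim section is descriptive: "To describe the accuracy and precision of the expectations of the clinicians of the effect of a fluid bolus at completion of the fluid bolus". The Statistical analysis section links it to a method: "The accuracy of the physicians’ estimations of the effect of a fluid bolus will be described using Bland-Altman methodology". Neither sentence mentions site.

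The regression is a further analysis: "Multiple regression analysis will also be performed adjusting for predefined confounding factors associated with hemodynamic changes". The list that follows has five items: vasopressor changes, sedation, diuretics, altered pacing and extra boluses. Neither site nor country appears in it.

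**The concern.** Site is the one grouping built into the design, and it can bear on everything the study compares. The physicians who state the expectations work at a particular ICU. The bolus is whatever that ICU gives, within a broad definition. The observed response is captured by that ICU's monitoring and record system.

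Two separate consequences follow if sites differ.

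- **Regression.** If an ICU uses more of a listed co-intervention and also has a different hemodynamic response or a different prediction error, a model without site assigns part of that ICU's difference to the co-intervention.
- **Primary outcome.** An overall mean bias is an average weighted by recruitment. If the sites' biases differ, its value depends on how many patients each site contributed, and the overall limits of agreement would show little sign of it.

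The protocol itself closes the adjustment set by calling it predefined and itemising it. Adding site after the data are seen would be a departure from that list. Adding it beforehand is not.

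**Working it through.** **No plan figure to reproduce.** The protocol states 100 patients but gives no SD, target precision, power or effect behind that number. The point disputes no stated figure, so what follows is an illustration under labelled assumptions, using mean arterial pressure in mmHg.

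**Inputs from the protocol:** N = 100; three sites, one of them Australian; no limit on any site's share; five listed confounders, none of them site.

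**Assumptions:** within-site SD of the prediction error 8, 10 or 12 mmHg; difference in mean bias between Australia and Sweden D = 0, 2, 5 or 8 mmHg, with the two Swedish sites taken as alike; Australian share w between 10% and 80%.

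**Step 1, sampling error of the overall bias.** Half-width = 1.96 × SD / √100.

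- SD 8: 1.96 × 8 / 10 = 1.57 mmHg
- SD 10: 1.96 × 10 / 10 = 1.96 mmHg
- SD 12: 1.96 × 12 / 10 = 2.35 mmHg

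**Step 2, effect of recruitment mix on the overall bias.** Relative to the Swedish bias, the overall bias is w × D. Between w = 0.1 and w = 0.8 it moves by (0.8 − 0.1) × D = 0.7 × D.

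| D (mmHg) | Shift in overall bias (mmHg) | Against the half-width of 1.57 to 2.35 |
|---|---|---|
| 0 | 0 | no effect |
| 2 | 1.4 | within sampling error at every SD |
| 5 | 3.5 | larger at every SD |
| 8 | 5.6 | larger at every SD |

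The shift equals the half-width at D = 1.57/0.7 = 2.2 (SD 8), 1.96/0.7 = 2.8 (SD 10) and 2.35/0.7 = 3.4 mmHg (SD 12).

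**Step 3, would the overall limits reveal it?** Half-width of the limits = 1.96 × √(SD² + w(1 − w)D²). At SD 10 and D = 0 this is 19.6. At D = 5 and w = 0.5 it is 1.96 × √(100 + 0.25 × 25) = 20.2. At D = 8 and w = 0.5 it is 1.96 × √(100 + 0.25 × 64) = 21.1. The limits barely widen, so an overall plot would not signal a site difference.

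**Step 4, the regression.** For a single yes/no co-intervention and a country difference D in the response, leaving country out biases the co-intervention's coefficient by D × (Australian share among patients with the co-intervention − Australian share among those without). This is zero if D = 0 or if the co-intervention is used equally in both countries. It can never exceed D in size. The protocol gives neither quantity, so no number can be put on it.

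**Step 5, precision of by-site results.** At SD 8, a site's mean bias has a 95% half-width of 1.96 × 8/√33 = 2.7 mmHg with 33 patients and 1.96 × 8/√10 = 5.0 with 10. For each limit of agreement, with standard error about SD × √(3/n), the half-widths are 1.96 × 8 × √(3/33) = 4.7 and 1.96 × 8 × √(3/10) = 8.6 mmHg.

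**The case against.** The strongest reply is that site terms and by-site tables are usually left to a statistical analysis plan, which may exist but is not shown, and that the list covers factors tied to hemodynamic change without claiming to name every covariate. That answers a complaint about missing detail in general. It does not fully answer this one, because the protocol fixes the adjustment set itself and leaves out a known design variable.

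Several stronger readings are tempting, and the documents do not support them.

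- A reader might infer that the headline accuracy does depend on which site recruits most. That is true only if accuracy differs by site, and nothing in the protocol says it does. Local care and data capture make a difference possible, no more.
- A reader might infer that the plan pools all 100 patients into one bias and one pair of limits. The protocol says only that Bland-Altman methodology is used. Pooling is inferred from the absence of any site component. Several variables in different units are predicted, so there cannot be a single bias, and not every patient need contribute to each variable.
- A reader might infer that a site term in the regression repairs the primary outcome. It does not. The regression is an additional analysis, and the Bland-Altman bias and limits would be unchanged.
- A reader might infer that a cap on each site's recruitment is needed. In a descriptive observational study that is a preference, and the point does not rest on it.

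It is also fair to object that by-site limits of agreement would be imprecise. That stands, and it shapes the fix.

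**Conclusion.** The point holds in conditional form. The predefined list omits site in a study where site can plausibly affect the expectation, the bolus and the measurement, and the protocol describes no display that would show whether it does.

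The size is unknown because it rests entirely on between-site differences that the protocol does not report. It is nil if there are none. Under the assumed range, a country difference of 2 mmHg stays within sampling error even for an extreme swing in recruitment, and one of 5 mmHg or more exceeds it. These results rest on assumed SDs of 8 to 12 mmHg, two alike Swedish sites and an Australian share anywhere from 10% to 80%.

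This is a modest weakness in a fixed analysis choice. It is not a demonstrated bias in the primary result. It is worth correcting because the correction is cheap and is cleanest before data are collected.

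**What to change.** Make two separate changes to the Statistical analysis section.

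1. Add site, as a fixed covariate with three levels, to the predefined confounder list for the regression.
2. For the primary outcome, show the mean bias by site, with its confidence interval and the number of patients, beside the overall Bland-Altman result for each variable. Label this a descriptive check, and note that by-site limits of agreement will be imprecise.

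The cost is two degrees of freedom in the regression (three levels minus one) and one descriptive table. No new data, no extra patients and no recruitment ceiling are needed. If an analysis plan already contains these items, the protocol's list only needs to be brought into line with it.

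### The regression omits the pre-bolus value although boluses are triggered largely by abnormal readings, so regression to the mean enters comparisons between patients, and no unbolused group separates it from the before-after change

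*Protocol*

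**What the plan says.** The Methods section describes an "Observational multi-center study of fluid administration in the ICU:s" and "Planned recruitment of 100 adult patients". Entry happens "When the treating physician chooses to give a fluid bolus (defined as 250 mL or more of fluids over 30 minutes or less"). The physician then ticks "pre-defined reasons to give fluids: hypotension, tachycardia, oliguria, low central venous pressure (CVP), high lactate levels", low venous saturation or low cardiac output. Most of these are readings of variables whose changes are listed as outcomes in the Aim section. Every studied patient receives a bolus, and no unbolused comparison is described.

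The primary outcome is the "accuracy and precision of the expectations of the clinicians of the effect of a fluid bolus at completion". The Statistical analysis section addresses it with Bland-Altman methodology and adds sensitivity, specificity, predictive values and AUC. Paired and repeated-measures comparisons are also planned. On regression it states: "Multiple regression analysis will also be performed adjusting for predefined confounding factors associated with hemodynamic changes". The named factors are all co-interventions or concurrent changes.

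Baseline data exist: "Measurements will be registered before the onset of the fluid bolus and until 60 min after completion of the fluid bolus".

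**The concern.** A variable that prompts treatment because it has just been read as too low or too high will, on average, be nearer its usual level at the next reading, whatever is given. Three results are exposed.

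- **Mean change after the bolus.** For the triggering variable it is the fluid response plus the rebound. Without a comparator the two cannot be separated.
- **Comparisons between patients.** A regression of change on expected response, or on the reason for the bolus, compares patients with different starting values. Without the starting value in the model, the coefficient absorbs the difference in rebound.
- **Discrimination.** A physician who expects MAP to rise whenever MAP is low will be right more often than chance even if fluid does nothing.

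The protocol speaks of the effect of the bolus and of clinicians' ability to predict the response. Both phrases invite a reader to attribute the rebound to fluid or to judgement.

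**Working it through.** The protocol gives no variance, correlation or expected change, so there is no figure of its own to reproduce. Everything below except n = 100 is assumed. The true fluid effect is set to zero throughout. The trigger levels are modelling inputs, not clinical thresholds.

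**Step 1: expected rebound.** For a normal variable with mean μ, SD σ and before-after correlation r, selected because it lies below c:

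rebound = (1 − r) × σ × φ(a)/Φ(a), with a = (c − μ)/σ.

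Take MAP with μ = 75, σ = 10, c = 65. Then a = −1, φ/Φ = 0.2420/0.1587 = 1.525, and the selected patients lie 15.25 mmHg below the mean (at 59.7).

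- r = 0.9: 0.1 × 15.25 = 1.53 mmHg
- r = 0.8: 0.2 × 15.25 = 3.05 mmHg
- r = 0.7: 0.3 × 15.25 = 4.58 mmHg
- r = 0.5: 0.5 × 15.25 = 7.63 mmHg

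Simulation agrees (1.51, 3.03, 4.58, 7.62). Over triggers of 60, 65 and 70 the range is 1.1 to 9.7 mmHg. If all 100 patients were selected on MAP, a before-after test at two-sided 5% would be significant with probability 0.74 to 1.00 (normal approximation). That is a worst case, because the reasons for a bolus are mixed.

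**Step 2: what adding the baseline does.** Same model, c = 65. The mixed cohort is half triggered by low MAP and half not selected on MAP.

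| r | Coefficient for MAP-triggered, no baseline (mmHg) | With baseline | AUC, rule: MAP-triggered | AUC, ranking by baseline MAP |
|---|---|---|---|---|
| 0.9 | 1.52 | −0.01 | 0.57 | 0.61 |
| 0.8 | 3.03 | −0.04 | 0.60 | 0.65 |
| 0.7 | 4.58 | 0.04 | 0.62 | 0.68 |
| 0.5 | 7.66 | 0.02 | 0.65 | 0.74 |

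Response here means a rise of at least 5 mmHg. The spurious between-patient difference disappears once the baseline is in the model. In a cohort selected only on low MAP, the mean change does not move: 4.58 mmHg with or without the baseline (r = 0.7).

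**Step 3: a second set of assumptions.** Mean MAP 70, between-patient SD 8, within-patient SD 5, 6 or 8, so r = 64/(64 + 25) = 0.72, 64/100 = 0.64 and 64/128 = 0.50. Trigger below 65; response is a rise of at least 10%; 60% of boluses are for low MAP.

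- Apparent rise in those below 65: 3.1, 4.1, 6.2 mmHg. About 34%, 41% and 51% count as responders.
- AUC of a rule that expects a rise only when MAP is low: 0.65, 0.66, 0.68 if every other bolus has MAP of 65 or more. If the others are unselected on MAP, it is 0.62 to 0.64 when the rule follows the reading and 0.60 to 0.62 when it follows the stated reason.
- Coefficient for an expected rise, others unselected: 3.1 to 6.2 mmHg without the baseline, about 0 with it.

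**Step 4: averaging pre-bolus readings.** With the trigger reading and five earlier independent ones, the rebound is divided by 6: 3.1/6 = 0.5 up to 6.2/6 = 1.0 mmHg. Real readings are autocorrelated, so the gain would be smaller.

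**Step 5: Bland-Altman.** Bias = mean expected change − (mean fluid response + mean rebound). The rebound lowers this difference. It brings the bias nearer zero for physicians who expect too much and further from zero for those who expect too little.

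**The case against.** The strongest reply is that the regression is a supplementary analysis. The primary outcome asks how far expectations are met, and the rebound is part of what is observed, so describing agreement between expected and observed change is no error. Covariates enter neither the Bland-Altman analysis nor an unadjusted AUC. This stands, and it limits the point to between-patient regression results, the reading of the mean change, and the interpretation of discrimination.

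Some stronger conclusions are tempting but not supported:

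- *That the missing covariates cause regression to the mean.* The cause is selection without a comparator. Step 2 shows that the baseline term leaves the overall mean change untouched.
- *That physicians' skill is inflated throughout.* In Bland-Altman the shift can go either way. The credit arises in sensitivity, specificity and AUC, and current MAP is information that a physician may legitimately use.
- *That every outcome is extreme by selection.* The protocol lists several reasons, and a bolus for oliguria does not select on MAP.
- *That bolus volume, fluid type or site belong to the same fault.* The bolus is "defined as 250 mL or more of fluids over 30 minutes or less", so its volume may vary, but none of these three has a bearing on regression to the mean.

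The size is also uncertain. If decisions rest on sustained readings, r may be near 0.9 and the rebound about 1 to 2 mmHg. Finally, a SAP that is not shown may add covariates or define a baseline window. However, the protocol itself names its predefined list, and the pre-bolus value is not on it.

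**Conclusion.** The point holds in a limited form. Selection on abnormal readings is built into entry, there is no comparator, and the named covariates omit a registered value that drives much of the difference in change between patients. Regression coefficients for expected response or reason for the bolus are therefore partly artefact: about 1.5 to 7.7 mmHg of MAP at a trigger of 65 in the first model and 3.1 to 6.2 mmHg in the second (others unselected), falling to about 0 with the baseline included.

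For the triggering variable, the apparent mean rise with no fluid effect is about 1.5 to 7.6 mmHg (r = 0.9 to 0.5). A rule with no insight beyond low MAP has an AUC of about 0.60 to 0.68 in the second model, and 0.57 to 0.65 in the first, rather than 0.50. These sizes rest wholly on assumed variability, trigger and mix of boluses; only the direction follows from the design. The primary description of agreement survives, but its interpretation needs the changes below.

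**What to change.** 1. Add the pre-bolus value of the variable being analysed to the predefined covariates in the Statistical analysis section.
2. Where electronic readings exist, define the baseline as the mean of several readings before the bolus, with the last reading as a sensitivity analysis. This step is needed because covariate adjustment does not remove the rebound from the overall mean change.
3. Report physicians' sensitivity, specificity and AUC beside those of a prediction from the baseline value alone. The difference shows what judgement adds.
4. Describe results as change after the bolus, not as the effect of the bolus, and state that the Bland-Altman bias includes any rebound.

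The cost is one more model term with 100 patients, extraction of readings already in the electronic system, and a few changes of wording. No new measurement and no change in care is needed. Averaging earlier readings may lag behind a true deterioration, which is why the last reading is kept as a sensitivity analysis. Laboratory values ordered at clinicians' discretion will often have only one earlier reading; for these, items 1, 3 and 4 apply.
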